## **VI. Approach to multiple hypothesis testing**

### **A. Primary analyses**

- To address the issue of multiple hypothesis testing, we will report the following for each primary test:
  1. Coefficient, standard error, and nominal  $p$ -value
  2. Indication of significance from an analysis controlling the false discovery rate at 0.1. This analysis will be done separately for each of the two primary RHS variables (delay ability and the self-regulatory competence index). (see [Section X](#) for detailed methodology)
  3. Bayesian “best guess” and SE for each coefficient given the priors listed in [Section C](#) below (see [Section X](#) for detailed methodology)
- We will also report the results of an enrichment analysis that tests joint significance of our primary hypotheses using a Wald test. We will evaluate significance using an empirical  $p$ -value calculated from a distribution of Wald statistics created by randomly resampling the key independent variable from the sample (with replacement), repeating all analyses, and re-running the Wald test. We evaluate significance using a 0.05 empirical  $p$ -value threshold. We will run separate empirical Wald tests for each of the two primary RHS variables (delay ability and the self-regulatory competence index)

### **B. Secondary analyses**

- For analyses with secondary outcomes, we will report coefficients, standard errors, nominal  $p$ -values, and Bayesian “best guess” and SE for each coefficient given the priors listed in [Section C](#) below
- For secondary tests (i.e., comparison of diagnostic to non-diagnostic conditions) and secondary sets of independent variables, we will report coefficients, standard errors, and nominal  $p$ -values

### C. Priors for Bayesian analyses

- We will set our priors for Bayesian analysis based on the key independent variable in the primary analyses:
  - Correlations with delay ability (deviation in delay time measured in the marshmallow task): mean of prior distribution = 0.05
  - Correlations with multi-year self-regulatory competence index: mean of prior distribution = 0.15
- We assume a standard deviation of the prior correlation of 0.2 for all analyses
- See [Section X](#) for detailed methodology and discussion of priors

## VII. Ex-ante hypotheses and notes on analysis

- We hypothesize that behavior in the marshmallow delay task will not have much explanatory power on mid-life outcomes. Performance on the task is a noisy measure of self-control and the effect is diluted as subjects' life trajectories have likely changed in the 30-40 years since the marshmallow task. We hypothesize that we will not find statistically significant results in our primary analyses predicting mid-life outcomes from behavior in the marshmallow delay task
- We hypothesize that correlations with indices of self-control behavior over the first 40 years of life will have more predictive power than performance on the marshmallow task alone. These correlations are likely to be higher because: (1) self-control is measured as recently as late 30s, much closer to the mid-life outcomes than the marshmallow task, (2) these measures have been successful in earlier work predicting life outcomes, and (3) index scores tend to be more successful than single measures of individual differences since they average out more noise
- We expect that the self-regulatory competence index will have low correlation with the outcome variables
- In this wave of data collection, we have responses from 113 of the original 550 Bing participants. We recognize that attrition and media attention to previous results from this sample are important issues; however, we make no assumptions of how these issues may impact results
- The focus of this paper is limited to the relationships and variables outlined in this document. Future analyses may test hypotheses using additional variables from the same wave of data collection. The analyses we plan to do in this project will be restricted to predictions of the outcomes measured using the survey this team conducted. The approach to handling multiple testing problems outlined in this analysis plan is designed specifically for this set of analyses will not affect future analyses addressing different questions, using variables based on other waves, past and future, of data collection from the Bing sample

## VIII. Definitions

### A. Raw delay time

- Raw delay time (measured in seconds) taken from the subject's first delay-of-gratification experiment
- Delay time ranges from 1 second to 900 seconds (the maximum possible delay time for the study design)
- Delay times are categorized into 21 conditions to account for differences in study designs across subjects (e.g., spontaneous vs. suggested ideation, rewards exposed vs. obscured, type of rewards, type of ideation, etc.)

## **B. Expected deviation from predicted delay time (uncensored log seconds and seconds)**

- We believe raw delay times differ meaningfully across treatment conditions, by age, and by gender and therefore calculate each subject's expected deviation from the delay time predicted by a Tobit random effects model conditional on their age, gender, treatment condition, and accounting for the censoring of delay times at 900 seconds
- See [Section X](#) for detailed methodology

## **C. Self-control measured in 1984 (parent), 1993 (self), and 2003 (self)**

- Reports of self-control were assessed at three time points using a modified versions of the California Child Q-set (Block & Block, 1969) that was completed by participants' parents with respect to their children's self-control ability in 1984, and by the participants' themselves in 1993, and then again in 2003
  - Note on self-control scores in 1984: There were two follow up surveys, one in 1982 and one in 1984. At each follow-up, both parents (i.e., mother and father) were asked to complete the CCQ. So, CCQ scores from 1984 are actually based on between 1 (from 1 parent at one time point) and 4 (from 2 parents at 2 time points) responses. At each time point, the responses were first standardized within each rater (i.e., mother and/or father), and then all responses (again, between 1 and 4 total) were averaged
  - 1993 and 2003 CCQ data were standardized within participants prior to computing self-control indices
- The self-control index is made up of 31 CCQ items split into 6 subscales (attention, coping, goal pursuit, concern for others, delay, and general cognitive ability). The final index variable was created using expert ratings, responses from 191 Smith college students, and the Bing data in 84, 93, and 03
- A preliminary set of self-control CCQ items was selected based on three expert ratings of each item in the full q-set for its relevance to aspects of self-control. The 37 items deemed relevant were administered to an independent sample of Smith College students. A principal components analysis revealed that all but one of these items loaded positively on the first unrotated factor. The remaining 36 items were examined using a confirmatory principal component analysis using ratings obtained in 1984, 1993, and 2003. Five items were eliminated from the analysis due to failure to demonstrate consistent positive loadings on the first unrotated principal component. From the remaining 31 items, two subscales consisting of 3 items each were formed on face value for the items relation to delay of gratification and general cognitive ability. The remaining 25 items were then factor analyzed within the Smith sample using principal axis factoring and oblique rotation noting that we fully expect positive correlations among the subscale. The four oblique factors resulting from this analysis were preliminarily attention, coping, goal pursuit, and concern for others. The item content of these scales as well as the delay and general cognitive ability subscale are listed below:
  - Attention Subscale
    - *Is attentive and able to concentrate*
    - *Is planful, thinks ahead*
    - *Is restless and fidgety* (lower score corresponds to higher self-control; reverse scored)
    - *Is easily distracted* (lower score corresponds to higher self-control; reverse scored)
    - *Is reflective; thinks and deliberates before speaking or acting*
    - *Uses and responds to reason*
  - Coping Subscale
    - *Can recuperate or recover after stressful experiences*

- *Tends to withdraw and disengage when under stress* (lower score corresponds to higher self-control; reverse scored)
- *Tends to go to pieces under stress; becomes rattles and disorganized*
- *Overreacts to minor frustrations; is easily irritated and/or angered* (lower score corresponds to higher self-control; reverse scored)
- *Reverts to more immature behavior when under stress* (lower score corresponds to higher self-control; reverse scored)
- *Tends to become rigidly repetitive or immobilized under stress* (lower score corresponds to higher self-control; reverse scored)
- *Exhibits self-control when frustrated*
- *Tends to get sidetracked by minor setbacks or obstacles* (lower score corresponds to higher self-control; reverse scored)
- **Goal Pursuit Subscale**
  - *Is persistent in activities; does not give up easily*
  - *Is competent, skillful*
  - *Has high standards of performance for self*
  - *Is resourceful in initiating activities*
  - *Becomes strongly involved in the things I do*
  - *Is productive, gets things done*
- **Concern for Others Subscale**
  - *Shows concern for moral issues (e.g., reciprocity, fairness, and the welfare of others)*
  - *Can be trusted, is dependable*
  - *Is considerate and thoughtful of others*
  - *Is calm and relaxed; easygoing*
  - *Is curious and exploring; eager to learn and open to new experiences*
- **Delay Subscale**
  - *Settles for smaller but immediately available outcomes rather than pursuing larger ones* (lower score corresponds to higher self-control; reverse scored)
  - *Frequently yields to temptation* (lower score corresponds to higher self-control; reverse scored)
  - *Is unable to delay gratification; cannot wait for satisfactions* (lower score corresponds to higher self-control; reverse scored)
- **General Cognitive Ability Subscale**
  - *Genuinely values intellectual and cognitive matters*
  - *Has high intellectual capability*
  - *Is verbally fluent; can express ideas well in language*
- The following items were not included in the 1984 follow-up and thus are excluded from the 1984 self-control index
  - *Is easily distracted*
  - *Exhibits self-control when frustrated*
  - *Tends to get sidetracked by minor setbacks or obstacles*
  - *Is productive, gets things done*
  - *Is considerate and thoughtful of others*
  - *Settles for smaller but immediately available outcomes rather than pursuing larger ones*
  - *Frequently yields to temptation*
  - *Genuinely values intellectual and cognitive matters*

- Note: “Tends to spend extra money rather than save or invest” was excluded from consideration for the index as it is too descriptive of the primary outcome variables
- The items are aggregated in the following way:
  - Each item is transformed using the inverse-normal transformation
  - Transformed items are averaged at the year-subscale level giving equal weight to each available item
  - The subscale score is then transformed using the inverse-normal transformation
  - For subjects with a self-control measure in at least one year, missing subscales are imputed from subscale data in available years. For example, to impute a 1984 attention score for someone who has a 1993 and 2003 attention score, we run a regression of 1984 scores on 1993 and 2003 scores and use the estimated coefficients to predict the 1984 attention score for the individual. Similarly, for someone who is missing both 1984 and 1993 attention scores, we predict the 1984 attention score from a regression on 2003 attention scores
  - Imputed scores for each subscale are transformed using the inverse-normal transformation
  - Subscales are then averaged within each year (giving equal weight to each subscale) to obtain aggregate self-control indices in 1984, 1993, and 2003
- For the secondary analyses, we create two aggregate measures:
  - An aggregate self-control index across all three years is created by applying the inverse normal transformation to each year’s self-control index and averaging across the three years, giving each year equal weight
  - We also construct aggregate subscales of the self-control index across all three years by averaging the three transformed subscales, giving each year equal weight (e.g., to create the attention subscale, we average across the 1984, 1993 and 2003 transformed attention subscales)

#### **D. Self-regulatory competence: index of behavior to 2003**

- We will create a measure of self-regulatory competence as an index of behavior that includes the expected deviation from predicted delay time (in uncensored log seconds) and self-control indices in 1984, 1993, and 2003. The index will be an average of each of the four measures (transformed by the inverse normal transformation), giving equal weight to each measure. The final index will be re-transformed using the inverse normal percentile transformation to obtain a measure of persistent self-regulatory competence
  - Expected deviation from predicted delay time in uncensored log seconds
  - Self-control index in 1984
  - Self-control index in 1993
  - Self-control index in 2003
- This aggregate measure will only be calculated for subjects with at least one self-control score

#### **E. Age in months at time of original delay experiment**

- Subject’s age in months when first completed the marshmallow delay experiment

## F. Gender

- Binary variable for whether the subject is male
  - *What is your sex? Male/Female*

## G. Net Worth

- Net worth = sum of assets – sum of debt
- Assets
  - *What is the current balance or total value of financial assets held by your household in the following types of accounts: Checking accounts, Savings accounts, Money market accounts, Certificates of deposit (CDs), Tax-deferred retirement accounts (e.g., IRAs, 401(k) accounts, Keogh accounts), Other tax-deferred savings accounts (e.g., education savings accounts, health savings accounts), Bonds not included in tax-deferred accounts, Stocks not included in tax-deferred accounts, Other assets not listed above*
  - *Please indicate the total market value for each of the following types of assets. That is, what would they be worth if they were sold today? If you are not sure of the exact figures, please provide a rough estimate. Your primary residence, Additional residence(s) or vacation home(s), not including rental properties, Rental properties, Other real estate, Business(es) or farm(s), Vehicles (any cars, trucks, boats, trailers, motor homes, airplanes or other vehicles), Other assets such as trusts, commodities, valuable art, jewelry, coins, collectibles, or other items*
- Debt
  - *Please indicate the amount you currently owe for any of the following items. If you are not sure of the exact figures, please provide a rough estimate. Home mortgage for your primary residence, Second mortgage, home equity loans or lines of credit, or home improvement loans for your primary residence, Mortgage(s), home equity loans or lines of credit, or other loans for your secondary residence(s), Mortgage(s), home equity loans, lines of credit, or other loans for your rental property, Other real estate loans, Business or farm loans, Vehicle loans, Credit cards or other revolving accounts (only if you carry forward a balance; do not include balances that are paid off each month), Installment loans for major purchases (e.g., appliances or furniture), Educational loans, Other personal loans, Medical bills*
- Note: Three respondents were assumed to have filled in monthly mortgage payments rather than total amount owed. All three had high interest rates (6.5%) so we assumed they were unable to re-finance and therefore had <20% home equity. We assumed these respondents had 25 years left on a 30-year loan and were therefore paying almost all interest in their monthly payments. One respondent's implied debt (monthly payments \* 12 / interest rate) was more than the value of the home, so we assumed 0% home equity. For the other two respondents, we assume 10% home equity (midpoint between 0 and 20%)
- Note: Two respondents were assumed to fill in monthly vehicle payments rather than total amount owed. We calculate the outstanding balance assuming the respondent is 3 years into a 6-year loan
- Note: One respondent was assumed to fill in monthly education loan payments rather than total amount owed. We calculate the outstanding balance assuming the respondent is 15 years into a 20-year loan

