## J. Annual amount of interest above 6% on high cost debt

- Respondents selected an interest rate bucket for each type of debt. We assumed the interest rate is the midpoint of the selected category (i.e., if selected 5-8% bucket, the interest rate is assumed to be 6.5%)
- “High Cost Debt” is any debt for which the interest rate is greater than 6%
  - We chose the 6% interest rate threshold as an interest rate above which there is, for the most part, no good excuse to be paying that high an interest rate. We assume subjects with debt at an interest rate above 6% are either:
    1. Financially incompetent (e.g., have not refinanced their mortgage rates despite low interest rates in the last few years)
    2. In financial distress (e.g., have high leverage ratio on their collateralized debts or have bad credit)
- For each high cost debt category we calculate the amount of interest above 6% as the dollar amount of debt multiplied by the interest rate above 6%

$$\sum_{\text{All high cost debt categories}} (\text{interest rate} - 6\%) \times \text{total amount owed}$$

- Please indicate the amount you currently owe for any of the following items. If you are not sure of the exact figures, please provide a rough estimate. Home mortgage for your primary residence, Second mortgage, home equity loans or lines of credit, or home improvement loans for your primary residence, Mortgage(s), home equity loans or lines of credit, or other loans for your secondary residence(s), Mortgage(s), home equity loans, lines of credit, or other loans for your rental property, Other real estate loans, Business or farm loans, Vehicle loans, Credit cards or other revolving accounts (only if you carry forward a balance; do not include balances that are paid off each month), Installment loans for major purchases (e.g., appliances or furniture), Educational loans, Other personal loans, Medical bills
- Please indicate the interest rate for each of those items. If you are not sure of the exact figures, please provide your best estimate.

| 0-4%                  | 5-8%                  | 9-12%                 | 13-16%                | 17-20%                | 21-24%                | >24%                  |
|-----------------------|-----------------------|-----------------------|-----------------------|-----------------------|-----------------------|-----------------------|

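### The mortgage assumption for three respondents does not follow from its own loan terms, and the debt assigned to two of them conflicts with those terms

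*SAP*

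**What the plan says.** The first note on debt in SAP section VIII.G (Net Worth) states that "Three respondents were assumed to have filled in monthly mortgage payments rather than total amount owed". It then builds the replacement value in four steps.

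- Equity range: "All three had high interest rates (6.5%) so we assumed they were unable to re-finance and therefore had <20% home equity".
- Loan age: "We assumed these respondents had 25 years left on a 30-year loan", from which it concludes that they "were therefore paying almost all interest in their monthly payments".
- Screen: an implied debt is computed as monthly payments × 12 / interest rate. For one respondent this "was more than the value of the home, so we assumed 0% home equity".
- Remainder: "For the other two respondents, we assume 10% home equity (midpoint between 0 and 20"%).

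Section VIII.J codes each reported interest-rate bucket at its midpoint: "if selected 5-8% bucket, the interest rate is assumed to be 6.5"%.

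Mortgage debt enters net worth (VIII.G), net worth / permanent income (VIII.I) and annual interest above 6% (VIII.J). All three are primary outcomes with n=109 in section III.A. For vehicle and education loans with the same reporting problem, VIII.G calculates an outstanding balance from an assumed loan age and term. Section V plans a robustness check that drops respondents whose data rested on assumptions.

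**The concern.** Dividing twelve monthly payments by the annual rate gives the balance only if the whole payment is interest. With 25 years to run, a level-payment loan is already repaying appreciable principal, so the inference and the formula built on it look inconsistent with the stated term and rate.

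The formula decides which respondent gets 0% equity. The same terms also limit what the other two can owe, and the 10% equity assigned to them may fall outside that limit. If so, the recorded debt contradicts the plan's own premises in three of the eleven primary outcomes. Dropping the records as a robustness check does not correct the primary values.

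**Working it through.** **Inputs.** From VIII.G: rate 6.5%; 30-year loan with 25 years left, so 300 monthly payments remain; implied debt = 12 × payment / rate; assigned equity 0% (one respondent) and 10% (two). From VIII.J: 6.5% is the coded value for the 5-8% bucket. The payments and home values are not given. Write P for the monthly payment, V for home value and r = 0.065/12.

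**1. The plan's figure.** Implied debt = 12P / 0.065 = 184.6 P.

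**2. Interest share on the plan's terms.** Share of the next payment = 1 − (1 + r)^−300 = 1 − 0.198 = 0.802. So 80.2% is interest and 19.8% is principal.

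**3. Balance on the plan's terms.** P × [1 − (1 + r)^−300] / r = 0.802 × 184.6 P = 148.1 P. The ratio 184.6 / 148.1 = 1.247, so the screening figure is 24.7% too high.

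**4. Whether another convention rescues the wording.** With annual payments the interest share is 79.3%. In the first month of the 30-year loan it is 85.7%. A 95% share would need about 46 years left, longer than the loan itself. None supports the inference.

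**5. The two respondents given 10% equity.** The note singles out one respondent as having implied debt above home value, which implies that for the other two 184.6 P ≤ V. Then:

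- balance ≤ 0.802 V, so equity ≥ 19.8%;
- assigned debt = 0.90 V;
- excess ≥ 0.900 − 0.802 = 0.098 V, or 0.900 / 0.802 − 1 = 12.2% of the balance.

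The note also holds equity below 20%. Taken together, its premises leave only 19.8% to 20%, yet it uses the midpoint of 0 to 20%.

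**6. The respondent given 0% equity.** Here 184.6 P > V, so the balance exceeds 0.802 V. Assigned debt is 1.00 V.

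- If implied debt lies between 1.00 V and 1.247 V, assigned debt is too high, by at most 0.198 V.
- If it is above 1.247 V, assigned debt is not too high.

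**7. Sensitivity to the true rate.** The plan's figure stays at 184.6 P, because 6.5% is the coded rate; only the true balance changes.

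| True rate | Balance with 300 payments left | Overstatement by 184.6 P | Upper bound on balance for the two |
|---|---|---|---|
| 5% | 171.1 P | 7.9% | 0.927 V |
| 6.5% | 148.1 P | 24.7% | 0.802 V |
| 8% | 129.6 P | 42% | 0.702 V |

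At 5% the bound lies above 0.90 V, so the assigned 90% need not be too high.

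**8. Illustration in dollars.** Home values are assumed here, since the SAP gives none. At 6.5% the excess debt for each of the two is at least 0.098 V: about $39,000 at V = $400,000 and about $59,000 at V = $600,000. Interest above 6% changes by 0.5% of that, about $196 and $293 a year.

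**The case against.** The strongest reply is that these values are declared assumptions about three doubtful records. The implied debt is only a screen against home value; recorded debt is 100% or 90% of home value, so the 24.7% error does not enter the data as such. This is correct. A reader might infer from the formula that all three debts are inflated by a quarter, and the SAP does not support that.

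A reader might also infer that all three debts are overstated. For the 0%-equity respondent this depends on an implied debt that the SAP does not report, so it is possible but not shown.

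Nor is 9.8% of home value a minimum at every rate. It holds at 6.5% and fails near the lower end of the 5-8% bucket. One might expect a true 5% to make the screening figure 40% too high, but that would require putting 5% into the plan's formula as well. With the formula held at the coded 6.5%, the overstatement is about 8%.

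It can further be said that the note has two premises, equity under 20% and 25 years left, that pull apart, and that nothing in the document ranks them. This also stands: the annuity balance is better tied to the reported payment, but it is still an imputation. The equity premise is the less secure of the two, since the high rate behind it matches a bucket midpoint and may not be a rate anyone reported.

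Finally, the effect is small. At most 3 of 109 records are involved, outcomes are percentile-ranked (section II), and section V already repeats the analyses without such respondents. That limits the consequence, but it does not reconcile the primary values with the stated terms.

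**Conclusion.** The point holds in a limited form. The inference that payments are nearly all interest is wrong on the plan's own terms: the share is 80.2%, and the screening figure overstates the balance by 24.7%.

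For two respondents, the assigned debt exceeds what those terms allow by at least 9.8% of home value. This rests on a 6.5% rate, 300 level payments remaining, and the implied but unstated fact that their screening figure did not exceed home value. For the third, overstatement occurs only if implied debt was between 100% and about 125% of home value, which cannot be checked from the SAP.

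The affected outcomes are net worth, net worth / permanent income and interest above 6%. The effect on the rank-transformed coefficients is expected to be small. This is a correctable inconsistency in a prespecified rule and gives no reason to doubt the main results.

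**What to change.** In section VIII.G, compute each of the three balances from the reported payment with the annuity formula, at 25 years remaining and 6.5%: balance = payment × [1 − (1 + 0.065/12)^−300] / (0.065/12), which is 148.1 × payment. This is in line with the vehicle and education loan notes. Use the result in all three outcomes.

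Remove the inference about nearly all interest, and the 0% and 10% equity assignments built on it. State that the below-20% equity premise no longer sets the value, because the computed equity may fall outside that range.

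As a sensitivity check, show the balances at 5% (171.1 × payment) and 8% (129.6 × payment), the ends of the reported bucket. Keep the section V check that drops these respondents as an addition.

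The cost is a few lines of SAP wording and the recoding of three records. No new data are needed.
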